#### 9.2.2 Secondary outcomes

##### 9.2.2.1 Immunogenicity

- Breadth of  $\gamma$ -IFN Elispot cellular immune responses to gag at 2 weeks after the final immunisation
- Frequency, breadth and magnitude of cellular immune responses at other time points (2 weeks after last DNA, 2, 12 and optionally 24 weeks after the first MVA +/- CN54rgp140/GLA-AF timepoint.
- CD4+ and CD8+ T-cell responses to HIV peptides as measured by ICS. The frequency and the functional quality of vaccine induced T cell responses will be studied at different time points
- The magnitude of T cell proliferative responses to HIV peptides at different time points.
- The frequency and magnitude of systemic IgG and IgA binding antibody responses to HIV antigens of other clades at other time points.

Other assays of antibody phenotype/function may include, but will not be limited to: the duration and avidity of envelope specific binding antibody responses, the frequency and titre of ADCC responses, the frequency and titre of ADCVI responses, the breadth of Envelope specific antibody responses, the frequency and titre of binding V1V2 specific IgG antibodies (linear and/or scaffolded protein) and the extent to which systemic antibodies bind to CD4.

### 9.2.2.2 Safety

- Any grade of adverse event that occurs in a participant that has received at least one immunisation.

## 9.3 Sample size

One hundred and eighty (180) individuals will be randomised to an active product group for the purpose of the analysis, with a further 18 individuals randomly allocated to receive saline for the purpose of blinding the laboratory and clinical staff and to reinforce the message that participants should not consider themselves protected against HIV. There will be two randomisations, the first to compare the three DNA treatment groups, each of which will have approximately 60 participants, and the second to compare two groups, namely MVA-CMDR given with CN54rgp140/GLA-AF and MVA-CMDR alone, each of which will have approximately 90 participants.

### Endpoint considerations for the purpose of calculating sample size

The primary endpoints for the first and second randomisations can be expressed as a proportional outcome, such as the proportion of responders, or as a summary characteristic of a continuous outcome, such as the mean or median magnitude of the SFC response to any CMDR pool, or the mean or median titre of binding or neutralising antibodies. A further example of a proportional outcome would be the proportion of subjects that had a clinically relevant cellular response AND a clinically relevant antibody response. For the purpose of calculating sample size we considered two possibilities:

#### ***Continuous variable (Magnitude of cellular response)***

An important difference in the magnitude of cellular responses will be defined as a doubling of mean SFC/ $10^6$  response in any CMDR pool, excluding the negative responders.

#### ***Proportion (Frequency of responders)***

An important difference in proportions will be defined as a 30% absolute difference in the frequency of responders by group.

### Statistical assumptions

Alpha will be reduced to 2.5% ( $p=0.025$ ) to adjust for multiple comparisons of the first randomisation, and will be 5% for the second randomised comparison. The following tables illustrate the power to detect a difference in a continuous variable or proportion with 60 or 90 subjects per group, using magnitude of response, and frequency of responders respectively.

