## 2.3 Rationale for design and objectives

A variety of strategies have been employed to enhance the efficiency of DNA priming including addition of adjuvants such as cytokines and methods to improve delivery including needle free devices such as the Biojector and Zetajet® and/or electroporation using devices such as the ID Derma Vax™.

The primary aim of the first randomisation is to assess the impact of electroporation (by Derma Vax™) used in combination with the needle free Zetajet® for DNA delivery after priming three times with 600µg DNA in a concentration of 3mg/ml (2 shots) or 600 µg DNA in a concentration of 6mg/ml (1 shot) followed by boosting twice with MVA-CMDR. The safety and immunogenicity of each of these regimens will be compared to 600 µg DNA in a concentration of 3mg/ml (2 shots) administered with the needle free Zetajet®, but without electroporation, a schedule that was employed in TaMoVac 01, and which was not significantly less immunogenic than the higher dose of 1000µg DNA. Administration of the DNA vaccine in a higher concentration (6mg/ml) as compared to the 3mg/ml concentration applied in TaMoVac 01 will reduce the overall number of shots in order to deliver the vaccine. An overall lower DNA dose priming as well as a reduction of shots for vaccine administration would make the DNA vaccine and delivery more feasibility and economic.

Within sub-studies knowledge and perception towards HIV vaccine trials in the recruitment communities will be assessed. Recruitment and acceptance for HIV vaccine trials are largely dependent on the knowledge, perceptions and attitudes towards HIV vaccine development within the volunteers’ communities. Following experiences of HIV Vaccine trials in Mbeya (RV 172 and TaMoVac I) and Dar es Salaam (HIVIS-03 and TaMoVac I) members of the communities have misconceptions about HIV Vaccine trials thereby posing challenges towards recruitment and retention of trial participants. As these trials aim to eventually lead to efficacy studies being conducted within the communities, assessing community knowledge, perceptions and recommendations for strategies that will effectively engage volunteers in HIV Vaccine trials will help to establish trustful relations with trial researchers, minimizing misconceptions and consequently improving recruitment and retention of trial volunteers.

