#### **Power to detect a range of differences in a proportion:**

| Increase in absolute difference (control to group of interest) | Power when n=60 per group | Power when n=90 per group |
|----------------------------------------------------------------|---------------------------|---------------------------|
| 40% to 70%                                                     | 86                        | 98                        |
| 40% to 60%                                                     | 48                        | 77                        |
| 50% to 80%                                                     | 89                        | 99                        |
| 50% to 70%                                                     | 50                        | 78                        |

60 participants per group provides adequate power ( $\geq 85\%$ ) to detect a doubling in mean magnitude or to detect a 30% absolute difference in the proportion of responders however the latter is defined. However, there is insufficient power to detect smaller differences, which could still be clinically meaningful. Ninety participants per group also provides adequate power for detecting a 75% increase in the magnitude of immune responses.

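### Section 9.3 plans both comparisons with Group I at 2.5% each, a valid single-step split; Holm's procedure would keep familywise error at 5% and gain power when both electroporation arms work

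*Protocol*

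**What the plan says.** The alpha appears in section 9.3, under Statistical assumptions: "Alpha will be reduced to 2.5" per cent, given there as the adjustment for having several comparisons in the first randomisation. The level for the second randomisation is 5%. A further sentence ties these levels to the power tables: "The following tables illustrate the power to detect a difference in a continuous variable or proportion with 60 or 90 subjects per group". Sidedness is not stated.

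Section 9.3 describes the first randomisation as "the first to compare the three DNA treatment groups, each of which will have approximately 60 participants". Section 2.3 says which comparisons are meant: the two electroporation regimens are introduced, and then "The safety and immunogenicity of each of these regimens will be compared to 600 µg DNA in a concentration of 3mg/ml (2 shots", the regimen given without electroporation. That makes two comparisons, II v I and III v I.

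After the tables, 9.3 finds 60 per group adequate (at least 85% power) for a doubling or a 30-point difference, but says that "there is insufficient power to detect smaller differences, which could still be clinically meaningful". Section 9.5.2 names rank tests for magnitude and Fisher's exact test for proportions, and leaves the detailed methods for comparing groups to the SAP. No step-down or other stepwise rule appears anywhere in the protocol.

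**The concern.** Read plainly, 9.3 has each electroporation arm tested against Group I at 2.5% whatever the other comparison shows. Holm's procedure starts at the same place, with the smaller p-value tested at 2.5%. If that is significant, the other is tested at 5%. Familywise error stays at or below 5%, and every rejection made under the equal split is also made under Holm.

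The extra rejections arise when both arms differ from Group I. That is the situation the protocol expects: section 2.3.1 hypothesises that electroporation improves priming and that the higher concentration gives responses comparable to the lower one, so Groups II and III should both exceed Group I. At stake is the chance of showing this for each arm, and for both delivery options together, with the 60 per group already planned.

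**Working it through.** **Inputs.** From 9.3: n = 60 per group, SD = 0.5 on the log10 scale, a doubling (log10 2 = 0.3010) or a 75% increase (log10 1.75 = 0.2430), and responders 40% v 70%. Alpha is 0.025 per comparison. The tests come from 9.5.2. All 60 per group are taken to contribute, as in the protocol's own table.

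**Reproducing the protocol's figures.** Two-sided normal approximation: power = Φ(δ / (σ√(2/n)) − z₁₋α/₂).

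- Standard error: 0.5 × √(2/60) = 0.0913. Critical value at α = 0.025: 2.241.
- Doubling: 0.3010/0.0913 = 3.298; Φ(3.298 − 2.241) = 85.5%. Protocol: 85.
- 75% increase: 0.2430/0.0913 = 2.662; Φ(0.421) = 66.3%. Protocol: 66.
- 50% increase: 37.7%. Protocol: 38.
- Proportions at n = 60 (pooled test): 86.7, 47.9, 89.8 and 49.8%. Protocol: 86, 48, 89 and 50.

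The n = 90 columns reproduce at two-sided 5%. A one-sided 2.5% test would give 91/76/49 for the first three. The planning basis is therefore a two-sided 2.5% for each comparison, that is 5% divided by two.

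**Equal split against Holm.** Three groups of 60 were simulated with Group I shared. Equal split: reject arm i if pᵢ ≤ 0.025. Holm: also reject arm i if pᵢ ≤ 0.05 and the other arm has p ≤ 0.025.

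| True effect | Test | Per arm, split → Holm | Both arms, split → Holm |
|---|---|---|---|
| Both double | rank | 82.5 → 87% | 72 → 81% |
| Both +75% | rank | 63 → 68% | 47 → 58% |
| Both 40% v 70% | Fisher | 81.5 → 86.9% | 70.6 → 81.4% |
| One doubles, other null | rank | 82.3 → 82.5% (active arm) | – |

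The split figures lie below the protocol's 85 and 86 because these tests are somewhat less powerful than the normal approximations behind its tables.

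The same comparison with z tests (correlation 0.5 through the shared Group I) gives, for a doubling in both arms, 85.5 → 89.3% per arm and 76.5 → 84.2% for both. The two gains agree: each extra Holm rejection turns a win on one arm into a win on both, so the gain for both arms is twice the gain per arm (2 × 3.8 = 7.6, against 84.2 − 76.5 = 7.7, the difference being rounding). A fixed 2.5% test would need about 67 per group to reach 89.3% per arm.

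**What does not change.** Holm's first step is the equal split's criterion, so the chance of detecting at least one arm is identical: about 93% with the rank test and 94.5% with z tests when both arms double. With no effect in either arm, familywise error is about 4.6% under both rules.

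**The case against.** The best case for the protocol is that nothing in it is wrong. An equal split is valid and conservative, and its power figures reproduce. The 2.5% stands among the sample-size assumptions, where sizing at Holm's first-step level is normal even if a step-down test follows, and 9.5.2 leaves the methods to the SAP. All of that stands. A reader might infer that the protocol forbids Holm, or that the split is an error; the text supports neither. What remains is that 9.3 gives 2.5% as the adjustment for these comparisons and offers no further step, so an SAP author who followed it would test both at 2.5%. Relaxing that after unblinding would look data-driven.

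A second objection is that the protocol never makes success on both arms a criterion; section 2.3 compares each regimen separately. That is fair, so the per-arm gain of 4 to 6 points is the primary measure, and the figure for both arms is supplementary.

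It would also be too much to say that the split loses power in every scenario, or that Holm cures the admitted weakness for smaller differences. For a 50% increase in both arms, z-test power per arm moves only from 37.7% to 42.1%. That shortfall comes mainly from the sample size.

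**Conclusion.** The point holds as an efficiency gain available at no cost in participants, not as an error or a contradiction. For II v I and III v I on a given primary endpoint, Holm controls the same 5%, never rejects less, and adds about 4 to 6 points of power per arm and 9 to 11 points for both arms at the effects tabulated above. It adds nothing to the chance of detecting at least one arm, and about 0.2 points for the active arm if only one works.

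These sizes assume 60 evaluable participants per group, SD 0.5 log10, equal effects in the two arms and two-sided tests. If magnitude is analysed among positive responders only, as 9.2.1.1 and 9.3 state, the numbers per group and the power under either rule would be lower.

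The 5% refers to two comparisons on one endpoint. If Group II v Group III were also tested at 2.5%, familywise error over the three pairs would be about 6.4%. The several primary immunogenicity results in 9.2.1.1 are a separate question that Holm on these two comparisons does not settle.

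**What to change.** Keep 2.5% as the conservative basis of the power tables. Add to section 9.3, and carry into the SAP before unblinding:

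*The two comparisons with Group I will be tested by Holm's procedure at a familywise two-sided 5% (smaller p-value at 2.5%; if significant, the other at 5%).*

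State that the rule applies to II v I and III v I on one primary endpoint, and does not extend to II v III or across the results listed in 9.2.1.1. Section 9.5.2 carries no alpha, so nothing there needs replacing.

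The cost is one sentence and no extra participants. The small downside is that a confidence interval not adjusted to the step-down rule may occasionally disagree with the test: an arm rejected at the 5% step could have a 97.5% interval that includes no difference. The protocol gives no interval level for the immunogenicity comparisons, so the SAP should say which level will be reported and that the Holm result decides.

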### Power to detect differences in a continuous variable:

| Increase in SFC          | Power when n=60 per group | Power when n=90 per group |
|--------------------------|---------------------------|---------------------------|
| 100% increase (doubling) | 85                        | 98                        |
| 75% increase             | 66                        | 90                        |
| 50% increase             | 38                        | 66                        |

Note: Based on  $\log_{10}$  transformed SFC, assuming a standard deviation of 0.5.

#### **Power to detect a range of differences in a proportion:**

| Increase in absolute difference (control to group of interest) | Power when n=60 per group | Power when n=90 per group |
|----------------------------------------------------------------|---------------------------|---------------------------|
| 40% to 70%                                                     | 86                        | 98                        |
| 40% to 60%                                                     | 48                        | 77                        |
| 50% to 80%                                                     | 89                        | 99                        |
| 50% to 70%                                                     | 50                        | 78                        |

60 participants per group provides adequate power ( $\geq 85\%$ ) to detect a doubling in mean magnitude or to detect a 30% absolute difference in the proportion of responders however the latter is defined. However, there is insufficient power to detect smaller differences, which could still be clinically meaningful. Ninety participants per group also provides adequate power for detecting a 75% increase in the magnitude of immune responses.

## **9.4 Interim monitoring and analyses**

Analyses will be performed at MUHAS by the Trial Statistician, who will be supported by the Statistical Mentor from the MRC CTU in London.

The accumulating safety data will be reviewed once by the DSMB (see also **section 15.5**) after half of the participants have completed the immunisation schedule. The DSMB will make a recommendation to the statistical team should any modifications to the safety analysis plan or statistical tables be required.

An unscheduled meeting of the DSMB may be required (**see section 7.6**), in which case the DSMB will make a recommendation to the Sponsor about whether or not to continue further immunisations in the trial.

## **9.5 Data analyses and presentations**

A full statistical analysis plan will be developed before the main analysis of the trial is performed. It will be based on the following populations and variables.

### **9.5.1 Participant populations**

- Intention-to-treat (ITT) population: all participants randomised and given at least one immunisation in the trial.
- Per-protocol (PP) population: all participants randomised and immunised with all scheduled immunisations, and who complete the trial with no major protocol deviations.

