## 7 ASSESSMENTS AND FOLLOW-UP

### 7.1 Duration of follow-up and schedule

An overview on study procedures are provided in the TaMoVac II Schedule (**Appendix 2**).

Participants will be required to make a minimum of 17 scheduled outpatient visits over the course of 52 weeks, with an optional extension to 18 visits over 64 weeks. Time 0 will start on the day of enrolment, which is also the day of randomisation and first immunisation.

Screening can take place up to 8 weeks (56 days) before time 0.

Immunisations will take place at weeks 0, 4, 12, 24 and 40.

Clinical safety follow up visits will be conducted 2 and 4 weeks after each immunization.

Long term immunogenicity and safety visits will be performed for a minimum of 12 weeks after the last immunization or are expected to be conducted until 24 weeks after the last immunization (optional).

Serum and peripheral blood mononuclear cells (PBMC) will be collected for immunogenicity at screening (Visit 2), enrolment (Visit 3), and weeks 14 (Visit 9), 26 (Visit 12), 28 (Visit 13), 42 (Visit 15), 44 (Visit 16) and 64 (Visit 18). Optionally the week 64 (Visit 18) immunogenicity tests will be performed at week 52 (Visit 17) if Visit 18 is not expected to be conducted.

Adverse events will be assessed during the enrolment visit following immunisation and at every visit thereafter. Routine laboratory safety parameters will be collected at screening, baseline, at every visit thereafter and at any other unscheduled visit if clinically indicated.

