#### 7.1.2 Visit windows

Immunisation visits are compliant with the protocol if they comply with the following target dates and visit windows:

DNA I (Visit 3, week 0): Day 0

DNA II (Visit 5, week 4): 28 days (+/-3) post DNA I

DNA III (Visit 8, week 12): 84 days (+/- 7) post DNA I

MVA I +/- CN54rgp140/GLA-AF (Visit 11, week 24): 84 days (+/-7) post DNA III

MVA II +/- CN54rgp140/GLA-AF (Visit 14, week 40): 112 days (+/-14) post MVA I +/- CN54rgp140/GLA-AF

If there is a delay >4 weeks, a decision will be made by the TMG as to whether immunisation will continue.

Safety follow up visits performed 14 days (2 weeks) after each immunization (Visits 4, 6, 9, 12 and 15) will be compliant with the protocol if they take place -3 to +3 days of the target date.

Safety follow up visits performed 28 days (4 weeks) after each immunization (Visits 7, 10, 13, 16) will be compliant with the protocol if they take place -5 to +5 days of the target date.

Long term immunogenicity and safety follow up visits are performed 84 days (12 weeks) and optional 168 days (24 weeks) after the last immunization and will be compliant with the protocol if they take place -14 to +14 days of the target date.

The primary endpoint and follow-up visits are scheduled for 2 and 4 weeks after the second MVA immunisation or at week 42 if immunisations have been discontinued will be compliant with the protocol if they take place  $\pm 7$  days either side of the target date respectively.

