### 9.2 Outcome measures

#### 9.2.1 Primary outcomes

##### 9.2.1.1 Immunogenicity

- The primary **immunogenicity** endpoint will be determined from the following results:
  - a positive response in the HIV peptide-specific  $\gamma$ -IFN Elispot assay using freshly isolated PBMCs collected 2 weeks after the final vaccination. A positive result will be defined as the numbers of spot-forming cells (SFC) more than four times the background (RPMI medium only) and > 55 SFC per million PBMC (Merck definition)
  - the magnitude of the  $\gamma$ -IFN Elispot assay response which will be restricted to those samples which have been defined as positive, as measured by the SFC 2 weeks after the final vaccination
  - the endpoint titre or concentration of systemic IgG CN54rgp140 specific antibodies measured 2 and/or 4 weeks after the final vaccination
  - the presence of neutralising antibodies to tier 1 and tier 2 viruses and the titre when these are present

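### The per-protocol set requires trial completion (week 52 or optional week 64), so the per-protocol immunogenicity analysis can lose valid week 42/44 results because of later events

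*Protocol*

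**What the plan says.** Section 9.5.1 of the protocol defines two populations. The ITT set is "all participants randomised and given at least one immunisation in the trial". The PP set needs all scheduled immunisations and is limited to those "who complete the trial with no major protocol deviations". Section 9.5 introduces these definitions as the foundation of the later SAP: "It will be based on the following populations and variables".

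The primary immunogenicity endpoints in Section 9.2.1.1 come before the end of the trial. ELISpot response is assessed "using freshly isolated PBMCs collected 2 weeks after the final vaccination". Binding antibody is based on "specific antibodies measured 2 and/or 4 weeks after the final vaccination". No time is given there for neutralising antibody. Section 7.1.2 agrees: "The primary endpoint and follow-up visits are scheduled for 2 and 4 weeks after the second MVA immunisation or at week 42", the latter for participants whose immunisations were discontinued.

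Follow-up continues beyond that. Section 7.1 sets a minimum of 17 visits over 52 weeks, "with an optional extension to 18 visits over 64 weeks". Section 7.7 accepts Visit 17, or optionally Visit 18, as the final visit.

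**The concern.** A per-protocol analysis is meant to show the effect in participants who followed the regimen up to the point of measurement. The rule in Section 9.5.1 goes further, because it makes membership depend on what happens after the measurement. Someone who received all immunisations, gave a valid sample at weeks 42 and 44 and then moved away before week 52 has not completed the trial and is removed. The same applies to a deviation judged major that occurs after week 44, such as joining another trial before the final visit, contrary to Section 5.4. None of these later events can change a result already obtained.

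Two things are at stake in the PP analysis. Precision falls, because valid results are discarded. The comparison also becomes conditional on behaviour after the endpoint, which could differ between groups.

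The rule is also out of step with the rest of the protocol. Section 5.5 sets its enrolment target by completion of the five immunisation timepoints, not by completion of follow-up. Section 7.6 makes the primary endpoint visit the minimum to be sought from participants who stop immunisation.

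**Working it through.** **Timing (Appendix 1 target days).** Visit 15 (week 42) is day 294, Visit 16 (week 44) day 308, Visit 17 (week 52) day 364 and Visit 18 (week 64) day 448.

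- From the week 42 sample to Visit 17: 364 − 294 = 70 days (10 weeks). To Visit 18: 448 − 294 = 154 days (22 weeks).
- From the week 44 sample to Visit 17: 364 − 308 = 56 days (8 weeks). To Visit 18: 448 − 308 = 140 days (20 weeks).

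So PP membership depends on at least 8 to 10 further weeks after the ELISpot and binding-antibody endpoints have been measured.

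**Inputs for power (Section 9.3).** 60 per group with alpha 2.5% for the first randomisation; 90 per group with alpha 5% for the second; SD 0.5 on the log10 scale; a doubling, log10(2) = 0.301; a 30-point difference in responders, 40% v 70%.

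**Formulas (two-sided, normal approximation).**

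- Means: power = Φ(δ / (σ√(2/n)) − z).
- Proportions: power = Φ((|p1 − p2| − z√(2p̄(1 − p̄)/n)) / √((p1(1 − p1) + p2(1 − p2))/n)), with p̄ the mean of p1 and p2.
- z = 2.241 for alpha 2.5%.

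**Reproducing the plan's figures, n = 60.**

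- Doubling: σ√(2/n) = 0.5 × √(2/60) = 0.0913; 0.301/0.0913 = 3.298; 3.298 − 2.241 = 1.056; Φ = 85.5%. The protocol states 85.
- 40% v 70%: (0.30 − 2.241 × √(0.495/60)) / √(0.45/60) = (0.30 − 0.2036)/0.0866 = 1.113; Φ = 86.7%. The protocol states 86.

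All 14 cells of the two power tables reproduce within 2 points by these formulas.

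**Effect of losing participants after the endpoint.** The protocol gives no such rate, so the losses below are assumptions. Each calculation starts from the full planned number and replaces n by n(1 − loss).

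| Assumed loss after endpoint | n from 60 | Doubling | 40% v 70% | n from 90 | 75% increase |
|---|---|---|---|---|---|
| 0% | 60 | 85.5% | 86.7% | 90 | 90.3% |
| 2% | 58.8 | 84.7% | 86.0% | 88.2 | 89.8% |
| 5% | 57 | 83.5% | 84.7% | 85.5 | 88.8% |
| 10% | 54 | 81.2% | 82.5% | 81 | 87.1% |
| 15% | 51 | 78.8% | 80.0% | 76.5 | 85.2% |

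With the PP set tied to the endpoint visit, participants lost only afterwards stay in, and the 0% row applies as far as this source of loss is concerned.

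**The case against.** The strongest reply is that little is lost. The ITT set has no completion condition, so every valid week 42/44 result remains in it, and nothing in Section 9.5 makes PP the primary analysis. A reader might infer that the trial discards endpoint data or that its main comparison is weakened. The documents do not support that; only one of the two sets is narrower than it need be.

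A reader might also infer that completing the trial has no determinable meaning because week 64 is optional. That goes too far. Section 7.1 makes 52 weeks the minimum, Section 7.7 accepts Visit 17 as final, and missing an optional visit is not naturally non-completion. Section 1.1.5 does give a total of 64 weeks for each participant, but the same section calls the 24-week follow-up optional. A clearer definition would help, but the ambiguity is limited.

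It can be said that the SAP will settle what counts as completion and as a major deviation. That is fair for the details. The completion condition itself, however, is a stated rule that Section 9.5 passes to the SAP, and nothing limits it to the period up to the endpoint.

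Finally, full follow-up matters for safety and durability. That is true, but it is no reason to exclude valid week 42/44 results from an immunogenicity comparison.

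The power figures also have limits. The loss rates are assumed. The PP set will not start from a full 60, since missed immunisations already exclude people, although Section 5.5 allows slightly more than 198 to be enrolled. The doubling criterion excludes non-responders. The planned tests are Fisher's exact and rank tests, not the normal formulas used here.

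**Conclusion.** The point holds for the PP analysis of immunogenicity and is minor. As written, the completion requirement removes valid week 42/44 results because of later loss or deviation. It serves no purpose for those endpoints and selects on post-endpoint events.

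The size depends on a late-loss rate that the protocol does not give. At 2% loss the cost for a doubling is under one percentage point of power (85.5% to 84.7%); at 15% it is about seven points (to 78.8%). These figures illustrate the precision lost and are not forecasts. Any selection effect cannot be sized from the documents.

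**What to change.** Amend Section 9.5.1 so that, for immunogenicity, the PP set is defined per endpoint: all scheduled immunisations received, an evaluable sample at that endpoint's visit (week 42 for ELISpot; week 42/44 for antibody, according to the reading used), and no major deviation up to that visit. Drop the trial-completion condition for these endpoints. Secondary endpoints at other times follow the same pattern, each with its own visit as the cut-off.

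This takes one or two sentences, ideally before the SAP takes over the current wording. It changes no visits or data collection. The small downside is that PP denominators may differ slightly between endpoints, so the number analysed should be reported for each.
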